#### Clinical trials

No study analysing the interest of MR antagonists on the prevention of CsA nephrotoxicity in humans has been published to date.

Only one study, in a transplanted patient with proteinuria despite double-blockade of the Renin-Angiotensin-Aldosterone System (RAAS) (by an angiotensin-converting enzyme inhibitor (ACE inhibitor) and Angiotensin II Receptor Antagonist (ARA2)) reported the efficacy of the addition of spironolactone on proteinuria (Gonzalez Monte *et al.*, 2010).

### **2.3. Summary of the benefits (if applicable) and the expected and known risks for subjects taking part in the study**

The expected benefits for patients participating in this study, taking into account its short duration, are small.

The expected benefits for society are essentially the possibility of carrying out a further study on the efficacy of eplerenone for the prevention of CsA nephrotoxicity. Currently, there are no drugs that can limit the renal toxicity of CsA. The aim of this future study will be to investigate the effect of eplerenone on the loss of renal function of renal transplant patients treated with CsA: the effect could be a longer life-expectancy of renal transplants and thus a lower cost (compared to a return to extra-renal dialysis or even a new transplant). These beneficial effects could be shared by patients participating in a prospective study comparing eplerenone with placebo.

The adverse events linked to the use of MR antagonists can be divided into ionic effects (hyperkalaemia and hyponatremia via their diuretic effect) and anti-androgenic effects (gynecomastia, problems with the menstrual cycle, impotence, etc...) (Bertocchio and Jaisser, 2010, Bertocchio *et al.*, 2011). The use of MR antagonists is usually not advised in patients with renal failure due to the increased risk of hyperkalaemia, particularly if another RAAS antagonist is added.

In France, there are two MR antagonists available on the market: spironolactone and eplerenone. The half-life of spironolactone is between 14 and 16 hours while that of eplerenone is between 4 and 6 hours. These two molecules are mainly metabolised by the liver after primary hepatic passage, but the metabolites of spironolactone also have a pharmacological effect by antagonising MR, glucocorticoid receptors and androgenic receptors (Struthers *et al.*, 2008, Epstein, 2003). Spironolactone has a strong affinity for MR, but eplerenone is more selective for MR. This selectivity is linked to the structure of the molecule (Sica, 2005). *In vitro*, nearly 400-times more eplerenone is required than spironolactone to antagonise other steroid receptors such as glucocorticoid receptors, androgen receptors and progesterone receptors, which are implicated in the development of adverse events in humans (Garthwaite and McMahon, 2004). The adverse effects of these two molecules have been compared in a randomised double-blind study (Parthasarathy *et al.*, 2011): the anti-androgenic effects, which are regularly a cause of termination of treatment, are clearly more frequent with spironolactone than with eplerenone.

Finally, a recent study highlighted an effect of spironolactone on glucidic metabolism that is not present with eplerenone: through its antagonistic action on the glucocorticoid receptor, spironolactone slightly increases cortisolemia, thus exposing patients to glycaemic imbalance. In a prospective study of more than 100 patients, eplerenone and spironolactone were compared for criteria relating to glucidic metabolism; in contrast to eplerenone, spironolactone significantly increased cortisolemia, the plasma concentration of adiponectin and glycosylated haemoglobin (HbA1c) (Yamaji *et al.*, 2010). Renal transplant patients, particularly those receiving CsA and/or corticoids, have an increased risk of diabetes (or NODAT, New-Onset Diabetes Mellitus After Transplantation). Although it has not been demonstrated that spironolactone induces diabetes, it appears wise to use a molecule that has less disruptive effect on glucidic metabolism in these patients.

### **2.4. Description and justification for the route of administration, the dose, the administration scheme and the duration of experimental treatments**

Eplerenone was granted MA for oral administration after the EPHEUS study (Pitt *et al.*, 2003) which demonstrated its efficacy in heart failure. It is administered daily as one dose.

In this tolerance study, we wish to investigate increasing doses of the two commercially available preparations (25 and 50 mg) in order to determine the therapeutic window between the minimal effective dose and the maximum tolerated dose (limiting this to a maximum of 50 mg/day) in renal transplant patients receiving CsA.

In a Spanish study in 11 patients (Gonzalez Monte *et al.*, 2010), 25 mg spironolactone achieved the primary objective of efficacy (proteinuria) in 3 months. The effect on kalaemia was maximal from the first month of treatment. We therefore think that we will see an increase in kalaemia in the first weeks of treatment (which will be maximal at the 4th week) and other adverse events in the following weeks: for this reason, we will carry out steps of 8 weeks (2 months).

## **2.5. Declaration indicating that the research will conform to the protocol, good clinical practice and current laws and regulations**

If the study is funded, the investigators agree to comply with the protocol for clinical research, good clinical practice and current laws and regulations.

## **2.6. Description of the study population**

In this tolerance study, we wish to determine the therapeutic window between the minimum effective dose and the maximum tolerated dose (limiting this to 50 mg/day maximum) in renal transplant patients receiving CsA with altered renal function (with an eGFR between 30 and 50 mL/min/1.73m^2).

The use of eplerenone is currently contraindicated in patients with renal failure defined by a creatinine clearance of <50 mL/min/1.73m^2 because there have been no specific studies in this population. However, a large multicentre study in cardiac failure (Zannad *et al.*, 2011) recently investigated the effect of eplerenone from stage II of the NYHA classification: nearly one-third of patients presented with chronic renal failure with an eGFR <60 mL/min/1.73m^2.

Similarly, the association of eplerenone with CsA is usually contraindicated because there has been no specific study in this population. By carrying out a study in patients receiving CsA with altered renal function, we will have the best conditions to reveal the major adverse event anticipated: hyperkalaemia.

We will select patients who have been transplanted for more than 2 years because this is when the doses of immunosuppressants and renal function are stable. Furthermore, from the end of the 2nd year of transplantation, the risk of acute rejection is low. We will exclude, for the same reasons, patients who have had an episode of acute rejection in the year prior to the date of inclusion. Furthermore, at 2 years after transplantation, nearly 50% of patients have histological signs of CsA toxicity (Nankivell *et al.*, 2003).

At an eGFR of <30 mL/min/1.73m^2, the lesions caused by CsA toxicity do not appear to be reversible. If the adverse effects of eplerenone are absent or acceptable, this molecule could be proposed to patients treated with CsA with a renal function >30 mL/min/1.73m^2.

Patients able to participate in the study should fulfil the following criteria (inclusion criteria):

- age ≥18 years on the date of inclusion
- possess full legal competence
- give their written consent
- be affiliated to a Social Security Regime
- have had a functional renal transplant for ≥2 years at the date of inclusion
- receiving treatment with CsA
- have a renal function estimated by the MDRD equation (Levey *et al.*, 1999) between 30 and 50 mL/min/1.73m^2

Patients able to participate in the study should not fulfil any of the following criteria (exclusion criteria):

- kalaemia  $\geq 5$  mmol/L at inclusion
- one or more previous episodes of severe hyperkalaemia ( $\geq 6$  mmol/L), whatever the cause
- be receiving treatment with a potassium exchange resin such as KAYEXALATE®
- an episode of acute rejection during the 12 months prior to inclusion
- be pregnant or not using effective contraception during the study
- uncontrolled arterial hypertension
- orthostatic hypotension
- systolic arterial pressure  $\leq 110$  mmHg
- cardiac failure in the 3 months prior to inclusion or cardiac failure (NYHA stages III or IV)
- severe liver failure (Child-Pugh class C)
- allergy to one of the components of eplerenone – INSPRA®
- be receiving treatment with spironolactone – ALDACTONE® or eplerenone – INSPRA®
- have a contraindication for which treatment cannot be suspended during the study: diuretic for hyperkalaemia, potassium salts, CYP3A4 enzyme inhibitor (such as itraconazole, ketoconazole, ritonavir, nelfinavir, clarithromycin, telithromycin, nefazodone)
- be receiving treatment with trimethoprim or digoxin
- be receiving treatment with alpha 1 blockers
- be receiving treatment with warfarin
- a malabsorption syndrome, an anomaly of galactose metabolism, galactase deficiency
- be receiving treatment with a non-steroidal anti-inflammatory drug, a lithium-based treatment, or any other nephrotoxic treatment
- be receiving treatment with double-blockade of the RAAS by the association ACE inhibitor and ARA2
- be a protected patient (under supervision, guardianship, placed under the protection of the law..)

### 3. STUDY OBJECTIVES

#### 3.1. Primary objective

This is a tolerance study aimed at determining whether tolerance to eplerenone, in a renal transplant patient treated with CsA and with an eGFR between 30 and 50 mL/min/1.73m^2, will allow the use of this molecule at a dose of 25 or 50 mg/day.

#### 3.2. Secondary objectives

The secondary objectives are to carry out a preliminary evaluation on the effect of eplerenone in this population on markers of renal function: essentially eGFR and proteinuria.

However, other markers of hydrosodium depletion (weight, fractional sodium excretion) will be studied in order to distinguish the part played by sodium depletion (diuretic effect of eplerenone) from the part played by the specific effects of eplerenone (anti-inflammatory, anti-fibrosis, anti-proteinuric effects, etc...).

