### **6.2. Associated medicines and treatments allowed or forbidden by the protocol, including rescue medications**

In cases of the development an adverse event, other treatments could be necessary for the realisation of this study:

- sodium polystyrene sulfonate (Kayexalate®): this is a powder for suspension administered orally or rectally and sold in bottles of 454 g with a measuring spoon; it is administered daily to treated hyperkalaemia

- sodium bicarbonate®: this consists of an extemporaneous capsule preparation containing 500 mg of sodium bicarbonate; it is administered daily to treat metabolic acidosis.

These treatments will be given to the patients by the promotor. The pharmacy associated with this study is the pharmacy of the CHU, Reims (Hôpital Robert Debré); the pharmacist responsible for the study is [name].

During this study, no medicine or treatment (except for those listed in the exclusion criteria) is forbidden but they should be mentioned as quickly as possible to the investigators and noted in the observation folder.

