#### **2) Metabolic acidosis**

In the case of mild metabolic acidosis (alkaline reserve  $\leq 20$  mmol/L but  $> 15$  mmol/L), the investigator will tell the patient to take 6 capsules of sodium bicarbonate 500 mg® the same day as well as measuring their alkaline reserve at the time of the next assessment.

In the case of significant metabolic acidosis (alkaline reserve  $\leq 15$  mmol/L) noted during the measurement after taking 6 capsules of sodium bicarbonate 500 mg® or spontaneously, treatment with eplerenone will be stopped, treatment with sodium bicarbonate 500 mg® doubled (12 capsules/day) and the alkaline reserve measured the following week.

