## 9. STATISTICS

### 9.1. Description of the statistical methods planned, including the timetable for any intermediate analyses if applicable

#### Global analysis

The analysis of the primary evaluation criterion will be carried out by a detailed breakdown as soon as the development of an adverse event(s) necessitates the termination of eplerenone treatment (see section 4.2). This will be a descriptive analysis.

The analysis of the secondary criteria will be descriptive and comparative between before and under eplerenone treatment.

Discontinuous variables will be expressed as percentages and continuous variables as the mean  $\pm$  standard deviation.

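### Both protocol rescue drugs add sodium while eplerenone continues, and the before/under comparison of weight and sodium excretion makes no allowance for it

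*Protocol*

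**What the plan says.** Protocol section 3.2 gives weight and fractional sodium excretion (FeNa) a specific task: "other markers of hydrosodium depletion (weight, fractional sodium excretion) will be studied in order to distinguish the part played by sodium depletion", the diuretic effect, from the specific anti-inflammatory, anti-fibrotic and anti-proteinuric effects.

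Section 6.2 names two treatments that may be needed if an adverse event occurs. One is "sodium polystyrene sulfonate (Kayexalate®): this is a powder for suspension administered orally or rectally". The other is a "capsule preparation containing 500 mg of sodium bicarbonate; it is administered daily to treat metabolic acidosis".

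Section 8.2 uses both before any decision to stop eplerenone. For kalaemia from 5.5 to below 6 mmol/L, the patient takes one spoon-measure of resin, then two if the recheck is still in that range. For alkaline reserve above 15 and up to 20 mmol/L, "the investigator will tell the patient to take 6 capsules of sodium bicarbonate 500 mg® the same day".

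Section 9.1 makes the analysis of the secondary criteria descriptive and "comparative between before and under eplerenone treatment". Section 9.4.2 only refers back to it. Neither mentions rescue.

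The information needed to identify rescued samples is collected. Resin use is a secondary criterion (section 4.1), and other treatments taken during the study are recorded (section 4.9). Section 5.2 excludes resin users at entry but not bicarbonate users.

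**The concern.** A before/under difference in FeNa or weight can be read as the diuretic effect only if nothing else that changes sodium handling starts between the two measurements. Here something else can start by protocol. Resin sodium can appear only on the “under” side, because resin users cannot enter. A bicarbonate dose given under section 8.2 is likewise new sodium after baseline.

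The two markers are pushed in ways that confuse the reading. Excreted rescue sodium raises FeNa and looks like natriuresis. Retained rescue sodium raises weight and hides depletion. The pair could therefore disagree for a reason unrelated to eplerenone, and there is no control arm to show it.

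Rescue is foreseeable. Section 12.2 names hyperkalaemia and metabolic acidosis as essentially the risks of the study, and section 8.2 gives every patient resin at inclusion. Section 2.4 expects kalaemia to peak at week 4, and D28 is one of the FeNa sampling days in Tables 1 and 2. At stake is how a preliminary secondary objective is interpreted.

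**Working it through.** The plan states no figure for this point, so there is none to reproduce. The check asks whether the rescue sodium is large enough to matter against the marker.

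**Inputs from the protocol**
- Bicarbonate while eplerenone continues: 6 capsules of 500 mg (sections 6.2 and 8.2).
- Renal function: 30 to 50 mL/min/1.73 m² (section 5.1), used here as GFR in mL/min.
- FeNa sampling: D0, D28 and D56 of each step (Tables 1 and 2).

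**Assumptions not in the protocol**
- Plasma sodium 140 mmol/L.
- Background sodium intake 100 to 200 mmol/day.
- Capsules taken daily up to the visit, with sodium balance reached.

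**Step 1: sodium load.** 6 × 500 mg = 3 g. With 84.0 g/mol for sodium bicarbonate, 3000 / 84.0 = 35.7 mmol sodium per day.

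**Step 2: filtered sodium.** GFR × 1.44 L/day × 140 mmol/L.

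**Step 3: added FeNa at balance.** 35.7 / filtered sodium.

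| GFR (mL/min) | Filtered sodium (mmol/day) | Added FeNa (percentage points) |
|---|---|---|
| 30 | 6048 | 0.59 |
| 40 | 8064 | 0.44 |
| 50 | 10080 | 0.35 |

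**Step 4: relative size.** 35.7 / 200 = 18% and 35.7 / 100 = 36%. For example, at GFR 40 and intake 150 mmol/day, FeNa moves from 150 / 8064 = 1.86% to 185.7 / 8064 = 2.30% with no diuretic effect.

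**Step 5: share of excreted sodium.** 35.7 / 235.7 = 15% and 35.7 / 135.7 = 26%. Most of the excreted sodium still comes from elsewhere.

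**Step 6: weight.** If one day's load were wholly retained as isotonic fluid, 35.7 / 140 = 0.26 L, or about 0.26 kg. This is an alternative to Step 3, which assumes full excretion, and the two do not add.

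**Step 7: group mean.** At GFR 40, each rescued patient among 31 moves the mean under-treatment FeNa by 0.44 / 31 = 0.014 points. The number rescued is not given, so the total shift is unknown.

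**Not computed.** The resin's sodium per spoon-measure is not in the protocol. The 12-capsule and 3-spoon doses in section 8.2 follow the stopping of eplerenone, when participation ends (section 4.6.1), so they are left out.

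**Does rescue overlap with sampling?** Section 8.2 words the rescue doses as taken the same day. However, section 6.2 describes both drugs as given daily, section 4.1 speaks of two resin spoon-measures per day, and section 8.2 later doubles the bicarbonate to 12 capsules per day. Section 8.2 also rechecks alkaline reserve only at the next assessment. Overlap with a D28 or D56 sample is therefore plausible but not certain. The protocol should reconcile these wordings, because the duration of rescue decides which samples are affected.

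**The case against.** The strongest reply is that section 9.1 is one general sentence and that handling of rescue medication is ordinary detail for a statistical analysis plan, which was not available here. Rescue use is recorded, so nothing prevents such a plan from dealing with it. This has force, and it keeps the point small. But the protocol itself states the purpose of the markers, the sodium-containing rescue and the before/under contrast, and as written these do not fit together.

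Other objections stand and limit the claim:
- A reader might infer that in rescued patients the markers simply measure the rescue's sodium. They do not: on the assumed intakes, bicarbonate supplies about 15 to 26% of excreted sodium.
- A reader might also infer that rescue goes to the patients with the largest sodium response. No section links kalaemia or alkaline reserve to the size of the natriuretic or weight response.
- Bicarbonate users may enter the trial. A stable dose already taken at D0 is not a change and does not bias the comparison.
- A rescue prompted by a visit's blood result comes after that visit's urine sample.
- Restricting the main comparison to rescue-free samples would select on a post-treatment event, and uncontrolled dietary sodium would remain. That counts against restriction as the main analysis, not against showing it beside the full one.

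**Conclusion.** The point holds as a modest, inexpensive improvement to a secondary analysis. Weight and FeNa are confounded by rescue sodium in rescued patients, and section 9.1 makes no allowance for it. For bicarbonate the size is 35.7 mmol/day, or 0.35 to 0.59 FeNa points at GFR 50 to 30 mL/min. This rests on daily intake up to the visit, sodium balance and plasma sodium of 140 mmol/L. The relative rise of 18 to 36% rests further on the assumed intake of 200 to 100 mmol/day. The resin adds an amount that the protocol does not allow one to compute.

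It would go too far to say that the separation of sodium depletion from specific effects fails altogether. The contamination is partial, the number of rescued patients is unknown, and section 3.2 calls the evaluation preliminary. The primary criterion, the stopping rules and the sample size of 31 are untouched.

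**What to change.** In section 9.1:
- Keep the before/under comparison of FeNa, natriuresis and weight on all samples.
- Flag each sample taken with current resin use, or with bicarbonate started or increased since D0. Do not flag a bicarbonate dose that is unchanged since D0.
- Show beside it a sensitivity comparison without the flagged samples.
- State that a rise in sodium excretion seen only in flagged samples will not be attributed to a diuretic effect.

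The cost is analysis wording only. Resin use and other treatments are already recorded, and no dose, visit or clinical rule changes. The sensitivity comparison has fewer samples and selects against patients with hyperkalaemia or acidosis, which is why both versions should be reported.

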#### 3.3. Objective of ancillary studies, if applicable

Subsequently, an ancillary study will evaluate the impact of eplerenone on biomarkers of inflammation (MCP-1), fibrosis (TGF- $\beta$ 1 and collagen IV, for example) or even renal damage (NGAL), which can be measured in the blood and urine of patients taking part in the study. The request made in the context of this local bid ('Appel d'Offre Local' 2011 (AOL 2011)) will not fund this ancillary study and a request for funds will be made specifically for this additional work.

### 4. STUDY CONCEPTION

#### 4.1. Evaluation criteria

##### **Primary criterion: *appearance of adverse events requiring the termination of treatment***

The adverse events requiring the termination of treatment that will be considered are:

- hyperkalaemia  $\geq 6$  mmol/L and/or hyperkalaemia  $\geq 5.5$  mmol/L under 2 spoon-measures/day of KAYEXALATE®
- acidosis revealed by an alkaline reserve  $\leq 15$  mmol/L
- systemic arterial hypotension revealed by a systolic arterial pressure  $< 100$  mmHg
- orthostatic hypotension defined by a decrease in systolic arterial pressure of  $> 20$  mmHg in the 3 minutes following standing
- acute renal failure defined by an increase in creatininaemia of  $> 30\%$  compared to its value at inclusion
- all other unexpected adverse events requiring the termination of eplerenone treatment

##### **Secondary criteria:**

- use of a potassium exchange resin
- systolic arterial pressure, diastolic, mean
- weight
- renal function (creatininaemia and creatinine clearance calculated using the MDRD formula)
- vascular resistance of the renal transplant
- natraemia, fractional sodium excretion ( $\text{FeNa}^+$ )
- natriuresis, creatininuria, kaluresis
- proteinuria, albuminuria

**Criteria for the ancillary study:**

- urine and plasma concentrations of NGAL
- urine excretion of TGF- $\beta$ 1, collagen IV and MCP-1

**4.2. Description of the study methodology****Study scheme (Figure 1)**

The tolerance study will be carried out by adapting the 2-step scheme of Simon (Simon, 1989) initially, and then by carrying out an increase in doses if tolerance is satisfactory.

From the data in the literature, it appears that the frequency of intolerance to treatment is <7% for a dose of 25 mg/day and <10% for a dose of 50 mg/day, which seems acceptable in this population and leads us to envisage a subsequent therapeutic trial. Conversely, its use does not appear possible if the respective frequencies are >15% and 20%, respectively.

In these conditions, for this tolerance study, we proposed a scheme which includes three successive stages combining the plan of Simon in two stages at a dose of 25 mg/day, and then an increase in dose to 50 mg/day with evaluation at a single time (Figure 1).

Under these conditions, the risk of not revealing unacceptable tolerance of eplerenone in this population is <10% and the risk of deciding, if tolerance permits, to not use it is 27%. There is a 60% chance of interrupting the study before the increase in dose if the hypothesis of unfavourable treatment is correct.

The advantages of the study scheme are that it will demonstrate unacceptable toxicity as early as possible and will detect a possible threshold effect between the doses of 25 mg/day and 50 mg/day which will allow the use of the lowest dose possible.

**Step 1:** 14 patients will be included in the first step, at an eplerenone dose of 25 mg/day. This stage will last 8 weeks. If  $\geq 3$  adverse events requiring the termination of treatment occur during these 8 weeks, the study will be stopped and the treatment will be considered to be too poorly tolerated to be used in this population. If <3 adverse events occur, we will proceed to step 2.

**Step 2:** This will consist of the addition of an additional 17 patients. All of the patients (14+17) will be treated with eplerenone at a dose of 25 mg/day for 8 weeks. If >4 adverse events requiring the termination of treatment occur during the 8 weeks, the study will be stopped and the treatment will be considered to be too poorly tolerated to be used in this population. If  $\leq 4$  adverse events occur, we will proceed to step 3.

**Step 3:** This will consist of an increase in the dose of eplerenone to 50 mg/day in all patients who participated in step 2. The duration of this step will be 8 weeks. If  $\geq 5$  adverse events requiring the termination of treatment occur, the study will be stopped and the treatment will be considered to be too poorly tolerated to be used in this population. If  $\leq 4$  adverse events occur, the tolerance of eplerenone treatment in this population will be considered to be acceptable.

[figure not shown]

**Figure 1. Study scheme** showing the different possibilities

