### 9.3. Size of the sample / population

#### 9.3.1 Calculation and/or justification of the number of subjects required

##### 9.3.1.1. Baseline hypothese(s) for this calculation:

According to data in the literature, the probabilities of hyperkalaemia developing during 8 weeks of eplerenone treatment are <7% with the 25 mg dose and <10% with the 50 mg dose (Gonzalez Monte *et al.*, 2010, Pitt *et al.*, 2003, Pitt *et al.*, 1999, Zannad *et al.*). We posed the alternative hypothesis that it is not useful to continue the study if the risk of hyperkalaemia is >15% with the 25 mg dose and 20% with the 50 mg dose.

The power for detecting an adverse event requiring the termination of treatment was fixed at 90%.

Under these hypotheses, it is possible to carry out a study in several steps by adapting the 2-step scheme proposed by Simon (Simon, 1989) in the following way:

First step: 14 patients will be included at the dose of 25 mg and followed for 8 weeks: if  $\geq 4$  patients experience an adverse event requiring the termination of treatment, the study will be stopped. In the opposite case, 17 additional patients will be included at the same dose for 8 weeks. If  $\geq 5$  patients out of the 31 have a limiting toxicity, the alternative hypothesis can be rejected and the study will be stopped; in the opposite case, the dose will be increased to 50 mg for 31 patients with a follow-up at 6 months. If at the end of this follow-up,  $\leq 4$  patients have a limiting toxicity with the 50 mg dose, the alternative hypothesis will be rejected and continuation of the study with eplerenone will be possible.

In these conditions, the probability of demonstrating a limiting toxicity greater than the fixed norms is 90.0%, the risk of stopping the study wrongly is 27.6%.

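### The stated 60% chance of stopping before the dose increase does not follow from the design: the rules behind 90.0% and 27.6% give 56%, and those printed in section 9.3.1.1 give 51%

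*Protocol*

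**What the plan says.** Section 4.2 sets the acceptable rates ("the frequency of intolerance to treatment is <7% for a dose of 25 mg/day and <10% for a dose of 50 mg/day") and the unacceptable ones: "Conversely, its use does not appear possible if the respective frequencies are >15% and 20%, respectively". It then describes three steps.

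- **Step 1:** "14 patients will be included in the first step, at an eplerenone dose of 25 mg/day". "If <3 adverse events occur, we will proceed to step 2"; with 3 or more the study stops.
- **Step 2:** 17 patients are added. The study stops if more than 4 limiting events occur among the 31.
- **Step 3:** the dose rises to 50 mg/day. Tolerance is unacceptable with 5 or more events.

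The same section summarises how the design performs. The risk of missing unacceptable tolerance is put below 10%; "the risk of deciding, if tolerance permits, to not use it is 27"%; and "There is a 60% chance of interrupting the study before the increase in dose if the hypothesis of unfavourable treatment is correct".

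Section 9.3.1.1 gives the matching overall figures: "the probability of demonstrating a limiting toxicity greater than the fixed norms is 90.0%, the risk of stopping the study wrongly is 27.6"%. Its step 1 boundary differs, however. There, four or more must be affected before the rule applies ("patients experience an adverse event requiring the termination of treatment, the study will be stopped. In the opposite case, 17 additional patients will be included"). Its step 2 boundary, 5 or more of 31, agrees with section 4.2.

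**The concern.** A three-step rule with fixed boundaries and fixed rates determines every one of these probabilities. If two of the three stated figures come from one set of boundaries, the third should come from it too. The 60% does not.

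It is the only figure in the protocol that says how often the design would halt before patients go to 50 mg/day when 25 mg/day is already unacceptable. Section 4.2 goes on to present early demonstration of unacceptable toxicity as an advantage of the scheme. Under section 4.10 the independent surveillance committee approves the protocol before the study starts, so the figure is in front of it as a property of the design.

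**Working it through.** **Inputs**

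- Unacceptable rates: 15% at 25 mg/day, 20% at 50 mg/day. Acceptable rates: 7% and 10% (section 4.2).
- Step 1: 14 patients, stop at r1 or more events, with r1 = 3 (section 4.2) or r1 = 4 (section 9.3.1.1).
- Step 2: 17 more patients, stop at 5 or more of 31, counted cumulatively.
- Step 3: stop at 5 or more of 31 at 50 mg/day.

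**Formulas**

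Let X1 ~ Bin(14, p), X2 ~ Bin(17, p), X3 ~ Bin(31, q), independent.

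- Probability of reaching step 3: C(p) = Σ over x < r1 of P(X1 = x) · P(X2 ≤ 4 − x)
- Probability of stopping before the dose increase: 1 − C(p)
- Probability of stopping at any step: 1 − C(p) · P(X3 ≤ 4)

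**Step A: reproduce the protocol's overall figures (r1 = 3)**

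- At 15%/20%: C = 0.4359 and P(X3 ≤ 4) = 0.2287, so 1 − 0.4359 × 0.2287 = 0.9003. The protocol states 90.0%.
- At 7%/10%: C = 0.8971 and P(X3 ≤ 4) = 0.8068, so 1 − 0.8971 × 0.8068 = 0.2762. The protocol states 27.6%.

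Both match. This fixes the protocol's own calculation: cumulative count in step 2, rates of exactly 15% and 20%, and r1 = 3.

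**Step B: stopping before the dose increase at p = 0.15**

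| x | P(X1 = x) | P(X2 ≤ 4 − x) | product |
|---|---|---|---|
| 0 | 0.1028 | 0.9013 | 0.0926 |
| 1 | 0.2539 | 0.7556 | 0.1919 |
| 2 | 0.2912 | 0.5198 | 0.1514 |
| 3 | 0.2056 | 0.2525 | 0.0519 |

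- **r1 = 3** (rows 0 to 2): C = 0.4359, so the chance of stopping is 56.4%. Step 1 contributes P(X1 ≥ 3) = 35.2% and step 2 the remaining 21.2%.
- **r1 = 4** (rows 0 to 3): C = 0.4878, so the chance is 51.2%. Step 1 contributes 14.7% and step 2 contributes 36.6%. The overall figures would then be 88.8% and 24.6%, not 90.0% and 27.6%.

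**Step C: look for a reading that gives 60%**

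| Reading, at p = 0.15 | r1 = 3 | r1 = 4 |
|---|---|---|
| Step 2 counts only new events, in patients still on treatment | 65.4% | 53.4% |
| Step 2 counts only new events, as if in 31 fresh patients | 68.0% | 57.8% |
| Cumulative count, with the first 14 exposed again | 81.9% | 80.6% |
| 5 or more judged on the 17 new patients alone | 41.6% | 23.1% |

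A single look at 5 or more of 31 gives 50.6%. None is within 2 points of 60%.

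A true rate of 15.6% would be needed to reach 60% with r1 = 3, and about 16.5% with r1 = 4.

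**The case against.** Four points can be made for the protocol.

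1. **Rounding.** The sentence sits in a descriptive paragraph, and 56.4% is 60% to the nearest ten. But nothing marks the figure as approximate, and the sentence before it gives 27%, to the percentage point.
2. **A composite hypothesis.** Unacceptable is defined as above 15%, so 56.4% is the value at the edge, and the chance rises to 62.1% at 16%. That is true, but the 90.0% is evaluated at exactly 15% and 20%. A reader will assume the same basis for the figure beside it.
3. **The step 2 count.** Section 4.2 has all 31 patients treated for 8 weeks in step 2 and counts events during those 8 weeks. Read literally, that is a count of new events only. With r1 = 3 it gives 65.4% or 68.0%, and 60% would then be an understatement. This is the strongest objection. However, with step 3 kept at 31 patients, the still-on-treatment version gives 92.1% and 29.2% overall, so it is not the rule behind 90.0% and 27.6%. What stands is that 56% depends on the cumulative count, and the text should say so.
4. **Small consequences.** The figure sets no boundary, sample size or error rate, and a patient with a limiting event leaves the study and is not escalated. This also stands and limits the weight of the point. Likewise, the 51% arises only from the conflict between sections 4.2 and 9.3.1.1, and the printing of 27.6% as 27% in section 4.2 is trivial.

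**Conclusion.** The 60% is wrong as written. On the calculation that yields the protocol's own 90.0% and 27.6%, the chance of stopping before the dose increase is 56.4%, which is 3.6 points lower. With the step 1 boundary of section 9.3.1.1 it is 51.2%, which is 8.8 points lower. The complementary chance of going on to 50 mg/day when the risk at 25 mg/day is 15% is 43.6% or 48.8%, against the implied 40%.

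This rests on independent patients, a true 25 mg/day risk of exactly 15%, a cumulative count over 31 patients at the end of step 2, and no loss to follow-up, as section 9.3.1.5 assumes. The error is modest and leaves the sample size of 31, the 90.0% and the 27.6% untouched, but it flatters the one stated safeguard against escalation. It should be corrected.

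**What to change.** First reconcile the step 1 boundary between sections 4.2 and 9.3.1.1, and state whether the step 2 count is cumulative. Which boundary applies is for the investigators to settle. Then restate the sentence in section 4.2 to match, with its assumption, on a cumulative count:

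- **3 or more of 14:** a 56% chance (35% in step 1, 21% in step 2) of stopping before the dose increase if the true risk at 25 mg/day is 15%. The 90.0% and 27.6% stand.
- **4 or more of 14:** a 51% chance (15% in step 1, 37% in step 2; the parts are rounded from 14.7% and 36.6%). The overall figures in sections 4.2, 9.3.1.1 and 9.3.1.3 then become 88.8% detection (11.2% missed) and 24.6% wrongly stopped.

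If step 2 is meant to count only new events, all three probabilities need recalculating on that rule. While the paragraph is open, print 27.6% in place of 27% if that figure still applies.

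The cost is one sentence once the boundary is settled, and a stated figure that is slightly less favourable.
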